## PEACOC

---

Patients should be carefully monitored for signs and symptoms of enterocolitis (such as diarrhoea, abdominal pain, blood or mucus in stool, with or without fever) and of bowel perforation (such as peritoneal signs and ileus).

- All patients who experience diarrhoea/colitis should be advised to drink liberal quantities of clear fluids. If sufficient oral fluid intake is not feasible, fluid and electrolytes should be substituted via IV infusion. For Grade 2 or higher diarrhoea, consider GI consultation and endoscopy with biopsy (to exclude microscopic colitis) to confirm or rule out colitis.
- For **Grade 2 diarrhoea/colitis**, administer oral corticosteroids.
- For **Grade 3 or 4 diarrhoea/colitis**, treat with intravenous steroids followed by high dose oral steroids.
- When symptoms improve to Grade 1 or less, steroid taper should be started and continued over no less than 4 weeks.
- **Type 1 diabetes mellitus (if new onset, including diabetic ketoacidosis [DKA]) or  $\geq$  Grade 3 Hyperglycaemia, if associated with ketosis (ketonuria) or metabolic acidosis (DKA):**
  - For **T1DM** or **Grade 3-4 Hyperglycaemia**
    - Insulin replacement therapy is recommended for Type I diabetes mellitus and for Grade 3-4 hyperglycaemia associated with metabolic acidosis or ketonuria.
    - Evaluate patients with serum glucose and a metabolic panel, urine ketones, glycosylated haemoglobin, and C-peptide.
- **Hypophysitis:**
  - For **Grade 2** events, treat with corticosteroids. When symptoms improve to Grade 1 or less, steroid taper should be started and continued over no less than 4 weeks. Replacement of appropriate hormones may be required as the steroid dose is tapered.
  - For **Grade 3-4** events, treat with an initial dose of IV corticosteroids followed by oral corticosteroids. When symptoms improve to Grade 1 or less, steroid taper should be started and continued over no less than 4 weeks. Replacement of appropriate hormones may be required as the steroid dose is tapered.
- **Hyperthyroidism or Hypothyroidism:**

Thyroid disorders can occur at any time during treatment. Monitor patients for changes in thyroid function (at the start of treatment, periodically during treatment, and as indicated based on clinical evaluation) and for clinical signs and symptoms of thyroid disorders.

  - **Grade 2 hyperthyroidism events (and Grade 2-4 hypothyroidism):**
    - In hyperthyroidism, non-selective beta-blockers (e.g. propranolol) are suggested as initial therapy.
    - In hypothyroidism, thyroid hormone replacement therapy, with levothyroxine or liothyronine, is indicated per standard of care.

- **Grade 3-4** hyperthyroidism:
  - Treat with an initial dose of IV corticosteroid followed by oral corticosteroids. When symptoms improve to Grade 1 or less, steroid taper should be started and continued over no less than 4 weeks. Replacement of appropriate hormones may be required as the steroid dose is tapered.
- **Hepatic:**
  - For **Grade 2** events, monitor liver function tests more frequently until returned to baseline values (consider weekly).
    - Treat with IV or oral corticosteroids
  - For **Grade 3-4** events, treat with intravenous corticosteroids for 24 to 48 hours.
  - When symptoms improve to Grade 1 or less, a steroid taper should be started and continued over no less than 4 weeks.
- **Renal Failure or Nephritis:**
  - For **Grade 2** events, treat with corticosteroids.
  - For **Grade 3-4** events, treat with systemic corticosteroids.
  - When symptoms improve to Grade 1 or less, steroid taper should be started and continued over no less than 4 weeks.
- **Stevens-Johnson syndrome (SJS) and toxic epidermal necrolysis (TEN):**

Cases of SJS and TEN, some with fatal outcome, have been reported in patients treated with pembrolizumab. For signs or symptoms of SJS or TEN, withhold pembrolizumab and refer the patient for specialised care for assessment and treatment. If SJS or TEN is confirmed, permanently discontinue pembrolizumab.
- **Other important potential risks include:** Based upon additional information received from the clinical study and postmarketing environments immune-mediated ADRs may be fatal and may occur after discontinuation of pembrolizumab.
- Arthritis adverse reactions have been identified during post-approval use of pembrolizumab. As these reactions are reported voluntarily from a population of uncertain size, it is not always possible to reliably estimate their frequency or establish a causal relationship to drug exposure.
- Immune-mediated irARs such as myocarditis, adrenal insufficiency, thyroiditis, uveitis, cholangitis, myositis, encephalitis and lung disease may occur. If a patient experiences any of these events, consult relevant medical specialists for management as per local policies.

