**Table 4: Management Guidelines for Drug-Related Adverse Events**

| General instructions: 
 
Corticosteroid taper should be initiated upon AE improving to Grade 1 or less and continue to taper over at least 4 weeks to less than or equal to 10mg (or equivalent) of prednisolone.
 
 NOTE:
For some immune-related AEs (please see list in the table below) pembrolizumab should be permanently discontinued in case of a G3 or G4 immune-related AE. 
 
For participants with Grade 3 or 4 immune-related endocrinopathy where pembrolizumab is withheld, pembrolizumab may be resumed when AE resolves to <math>\leq</math> Grade 2 and is controlled with thyroid replacement therapy (hypothyroidism), non-selective beta-blockers (eg, propranolol) or thionamides (hyperthyroidism) or in the case of hyperglycaemia, metabolic control is achieved (in case of T1DM).
 
 
 
For situations where pembrolizumab has been withheld, pembrolizumab can be resumed after AE has been reduced to Grade 1 or 0 and corticosteroid has been tapered (unless it is specified to permanently discontinue pembrolizumab in case of G3 or G4 immune-related AE in the table below). Pembrolizumab should be permanently discontinued if AE does not resolve within 12 weeks of last dose or corticosteroids cannot be reduced to <math>\leq 10</math> mg prednisolone or equivalent per day within 12 weeks.
 
For severe and life-threatening irAEs, IV corticosteroid should be initiated first followed by oral steroid. Other immunosuppressive treatment should be initiated if irAEs cannot be controlled by corticosteroids.
 
 |                                                                        |                               |                                                                                                                                                                                                                          |                                                                                                                                                                                                                                                                                                                                                                                                                                                                                               |

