|                                                                            | Grade 3 or 4                                                                                                                 | Permanently discontinue               | 
 
Administer corticosteroids (initial dose of 1-2 mg/kg prednisolone or equivalent) iv for 24-48 hours followed by oral taper
 
                 |                                                                                                                                                                                     |
| Type 1 diabetes mellitus (T1DM) or Hyperglycaemia                          | New onset T1DM or Grade 3 or 4 hyperglycaemia associated with evidence of $\beta$ -cell failure measured by insulin in serum | Withhold                              | 
 
Initiate insulin replacement therapy for participants with T1DM
 
Administer anti-hyperglycaemic in participants with hyperglycaemia
 
 | 
 
Monitor participants for hyperglycaemia or other signs and symptoms of diabetes.
 
                                                  |
| Hypophysitis                                                               | Grade 2                                                                                                                      | Withhold                              | 
 
Administer corticosteroids and initiate hormonal replacements as clinically indicated.
 
                                                      | 
 
Monitor for signs and symptoms of hypophysitis (including hypopituitarism and adrenal insufficiency)
 
                              |
|                                                                            | Grade 3 or 4                                                                                                                 | Withhold or permanently discontinue * |                                                                                                                                                                                               |                                                                                                                                                                                     |

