| Hyperthyroidism                                                            | Grade 2                                                                                                                      | Continue                              | 
 
Treat with non-selective beta-blockers (eg, propranolol) or thionamides as appropriate
 
                                                      | 
 
Monitor for signs and symptoms of thyroid disorders.
 
                                                                              |
|                                                                            | Grade 3 or 4                                                                                                                 | Withhold or permanently discontinue * |                                                                                                                                                                                               |                                                                                                                                                                                     |
| Hypothyroidism                                                             | Grade 2-4                                                                                                                    | Continue                              | 
 
Initiate thyroid replacement hormones (eg, levothyroxine or liothyronine) per standard of care
 
                                              | 
 
Monitor for signs and symptoms of thyroid disorders.
 
                                                                              |
| Myocarditis                                                                | Grade 1                                                                                                                      | Withhold                              | 
 
Based on severity of AE administer corticosteroids
 
                                                                                          | 
 
Ensure adequate evaluation to confirm etiology and/or exclude other causes
 
                                                        |

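### Section 9.5: Table 4 and the text below it conflict on the treatment of Grade 3-4 hyperthyroidism and on the trigger for Grade 3-4 hyperglycaemia

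*Protocol*

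**What the plan says.** Section 9.5 handles immune-related events twice, first in Table 4 and then in text below it, organised by event.

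**Hyperthyroidism.** The treatment column of Table 4 reads "Treat with non-selective beta-blockers (eg, propranolol) or thionamides as appropriate". This is printed against Grade 2, and the treatment cell for Grade 3 or 4 is blank. For Grade 3 or 4 the dosing column offers withholding or permanent discontinuation, which a footnote leaves to the investigator or treating physician. Under the general instructions, a patient with a Grade 3 or 4 endocrinopathy may resume at Grade 2 or below once controlled, for this event by "non-selective beta-blockers (eg, propranolol) or thionamides (hyperthyroidism". The text below the table divides treatment by grade. Under Grade 2 it says "In hyperthyroidism, non-selective beta-blockers (e.g. propranolol) are suggested as initial therapy". Under Grade 3-4 it says "Treat with an initial dose of IV corticosteroid followed by oral corticosteroids", followed by a taper that begins at Grade 1 or less and lasts at least 4 weeks.

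**Hyperglycaemia.** The Table 4 row covers new-onset type 1 diabetes, or Grade 3 or 4 hyperglycaemia with evidence of beta-"cell failure measured by insulin in serum". The action is to withhold. Insulin is named for type 1 diabetes; otherwise the entry is "Administer anti-hyperglycaemic in participants with hyperglycaemia". The heading in the text covers new-onset type 1 diabetes, or hyperglycaemia of Grade 3 or above with ketosis or metabolic acidosis. It continues: "Insulin replacement therapy is recommended for Type I diabetes mellitus and for Grade 3-4 hyperglycaemia associated with metabolic acidosis or ketonuria". The work-up is: "Evaluate patients with serum glucose and a metabolic panel, urine ketones, glycosylated haemoglobin, and C-peptide".

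**The concern.** Both parts of section 9.5 are addressed to sites. The introduction to the section assigns dose management to Table 4. The note under the table tells sites to observe the text as well and to check the current Investigator's Brochure. Nothing ranks the table against the text on treatment or on what defines the event.

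For hyperthyroidism, what is at stake is whether a patient with a serious event is given systemic corticosteroids, and which restart rule then applies. For hyperglycaemia, it is whether a patient falls under the row that carries the withhold instruction. Sites could manage the same event differently while each follows the protocol as written, which would blur the exposure and safety data for these events.

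**Working it through.** No arithmetic applies. The check is to set the provisions of section 9.5 side by side.

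**1. Grade 3-4 hyperthyroidism**

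| | Table 4 | Text below Table 4 |
|---|---|---|
| Treatment named at Grade 3-4 | Beta-blockers or thionamides, if the blank cell is merged with Grade 2 | IV then oral corticosteroids |
| Where beta-blockers appear | The row's only treatment entry; also in the restart condition for Grade 3-4 | Under Grade 2 only |
| Steroid taper | Not mentioned in the row | At least 4 weeks, starting at Grade 1 or less |

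The merged-cell reading is an inference, so it needs support. There are three grounds.

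- The pneumonitis, hypophysitis and nephritis rows show the same pattern: treatment printed once against the lower grade, with the higher-grade cell blank.
- Where treatment does differ by grade, as for liver enzymes, the table prints a separate entry for Grade 3 or 4.
- The Grade 3 or 4 endocrinopathy restart instruction presupposes control by beta-blockers or thionamides, which fits those drugs being the table's treatment at that grade.

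The hypophysitis row names corticosteroids. The table therefore does mention steroids for an endocrine event where it calls for them.

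**2. Which restart rule follows**

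The general instructions of Table 4 hold two rules that could apply to a patient withheld for Grade 3-4 hyperthyroidism and given steroids.

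- Endocrinopathy rule: resume at Grade 2 or below once controlled with beta-blockers or thionamides. It has no steroid condition.
- General rule: resume at Grade 1 or 0 with steroids tapered. Discontinue permanently if the event does not resolve within 12 weeks of the last dose, or if steroids cannot be brought to 10 mg or less of prednisolone daily within 12 weeks.

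A patient treated as the table suggests fits the first rule. A patient treated as the text directs has the event named in the first rule and the steroid course contemplated by the second. The protocol does not say which governs.

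**3. Grade 3-4 hyperglycaemia that is not new-onset type 1 diabetes**

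| Patient | Table 4 diabetes row | Text heading |
|---|---|---|
| Beta-cell failure and ketosis or acidosis | Met | Met |
| Ketosis or acidosis, no documented beta-cell failure | Not met | Met |
| Beta-cell failure, no ketosis or acidosis | Met | Not met |
| Neither | Not met | Not met |

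The two definitions part company in the second and third rows. The second is the more awkward. The text's work-up lists C-peptide but not serum insulin, which is the measurement the table's trigger names. A site that completes the work-up has therefore not obtained the test on which the withhold row depends.

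**4. Insulin**

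The table names insulin for type 1 diabetes only. The text recommends it also for Grade 3-4 hyperglycaemia with acidosis or ketonuria. This difference is milder, because an unspecified anti-hyperglycaemic does not exclude insulin.

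**The case against.** The strongest reply is that the hyperthyroidism conflict depends on a merged cell. Read strictly row by row, the table gives beta-blockers or thionamides at Grade 2 and nothing at Grade 3-4, which leaves room for the text. Table 4 is also a set of guidelines: its treatment column allows steroids and other therapies, and giving both drug classes would breach neither part. These points stand in part, and they make it too strong to say that following one part necessarily violates the other. But the strict reading leaves a Grade 3-4 restart rule that rests on drugs named for that grade in neither part, and the choice between the two restart rules stays open.

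A reader might go further than the documents allow in five ways.

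- **High-dose steroids.** The hyperthyroidism text gives no dose level. Among the event texts below the table, that description appears only for diarrhoea/colitis.
- **Whether a dose is withheld depends on the page read.** For these two events the text gives no pembrolizumab dosing instruction, and section 9.5 assigns dose management to Table 4. What remains is the gap in the trigger.
- **The trigger is unusable because Table 6 omits serum insulin.** Table 6 lists the trial's laboratory tests and is not a work-up for immune-related events. It also omits C-peptide, and section 9.5 allows additional tests. The point rests on the work-up in the text.
- **A restart at least one dose later under the text.** A 4-week taper is longer than a 3-week cycle, but the delay follows only if the general restart rule overrides the endocrinopathy rule, which is the open question.
- **Every Grade 3-4 hyperglycaemia is affected.** Both parts carry qualifiers and both include new-onset type 1 diabetes.

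Two further replies have some force. Withholding or stopping for Grade 3-4 hyperthyroidism is already discretionary, so some variation between sites is intended; that discretion does not extend to the differing treatment instructions. The catch-all row for other immune-related events may also take in a hyperglycaemia that misses the diabetes row, if it is judged immune-related. That does not restore agreement: at Grade 4 the catch-all row says permanent discontinuation, whereas the diabetes row says withhold.

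**Conclusion.** Section 9.5 is inconsistent as written on two serious events. For Grade 3-4 hyperthyroidism the treatments named differ, and the applicable restart rule is unclear once steroids are given. For Grade 3-4 hyperglycaemia outside new-onset type 1 diabetes the triggers differ, and the work-up omits the test named by the row that withholds treatment. The difference over insulin is secondary.

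The hyperthyroidism finding assumes that the blank Grade 3-4 cell in Table 4 is merged with Grade 2; the layout of other rows and the restart instruction support this. The current Investigator's Brochure, which sites must also check, is not available here and might settle some of it, but the protocol should not contradict itself. The protocol gives no event rates, so the number of patients affected cannot be estimated, and no effect on the 12-week primary endpoint is shown. The inconsistency should be corrected because it concerns safety instructions. No view is taken on which instruction is right.

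**What to change.** Reconcile the general instructions of Table 4, its hyperthyroidism and diabetes/hyperglycaemia rows, and the matching text in section 9.5, so that:

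- Grade 3-4 hyperthyroidism has one treatment instruction, printed explicitly against that grade in the table.
- One restart rule is named for a patient with an endocrinopathy who has received steroids.
- Grade 3-4 hyperglycaemia has one trigger, resting on tests that the stated work-up contains, and one statement of when insulin is used.

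Alternatively, add a sentence saying whether the table or the text prevails on treatment and event definition, and align the work-up with the trigger retained. The sponsor decides the clinical content. The cost is a wording amendment with no added visits; aligning the work-up may mean naming one test differently.

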## Management of Infusion Reactions:

## PEACOC

Signs and symptoms usually develop during or shortly after drug infusion and generally resolve completely within 24 hours of completion of infusion. Infusion-related reactions may present as allergic reaction (hypersensitivity), serum sickness, infusion and infusion-like reactions, cytokine release syndrome, or anaphylaxis. In the case of severe or life-threatening reactions, subsequent doses of pembrolizumab should not be administered.

Table 5 shows management guidelines for patients who experience an infusion reaction associated with administration of pembrolizumab (MK-3475).

**Table 5: Infusion Reaction Management Guidelines**

| NCI CTCAE v5 Grade                                                                                                                                                                                                                                                                                                                                                                  | Treatment                                                                                                                                                                                                                                                                                                                                                                                                                                                                                                                                                                                                                                                                                                                                                                                                       | Premedication at subsequent dosing                                                                                                                                                                                                               |
|-------------------------------------------------------------------------------------------------------------------------------------------------------------------------------------------------------------------------------------------------------------------------------------------------------------------------------------------------------------------------------------|-----------------------------------------------------------------------------------------------------------------------------------------------------------------------------------------------------------------------------------------------------------------------------------------------------------------------------------------------------------------------------------------------------------------------------------------------------------------------------------------------------------------------------------------------------------------------------------------------------------------------------------------------------------------------------------------------------------------------------------------------------------------------------------------------------------------|--------------------------------------------------------------------------------------------------------------------------------------------------------------------------------------------------------------------------------------------------|
| Grade 1
Mild reaction; infusion interruption not indicated; intervention not indicated                                                                                                                                                                                                                                                                                    | Increase monitoring of vital signs as medically indicated until the patient is deemed medically stable in the opinion of the investigator.                                                                                                                                                                                                                                                                                                                                                                                                                                                                                                                                                                                                                                                                      | None                                                                                                                                                                                                                                             |
| Grade 2
Requires infusion interruption but responds promptly to symptomatic treatment (e.g., antihistamines, NSAIDS, narcotics, IV fluids); prophylactic medications indicated for <=24 hrs                                                                                                                                                                               | Stop Infusion and monitor symptoms.
Additional appropriate medical therapy may include but is not limited to:
IV fluids
Antihistamines
NSAIDS
Paracetamol
Narcotics

Increase monitoring of vital signs as medically indicated until the patient is deemed medically stable in the opinion of the investigator.
If symptoms resolve within one hour of stopping drug infusion, the infusion may be restarted at 50% of the original infusion rate (e.g., from 100 mL/hr to 50 mL/hr). Otherwise dosing will be held until symptoms resolve and the patient should be premedicated for the next scheduled dose.
Patients who develop Grade 2 toxicity despite adequate premedication should be permanently discontinued from further trial treatment administration. | Patient may be premedicated 1.5h ( $\pm$ 30 minutes) prior to infusion of pembrolizumab (MK-3475) with:
Antihistamines 50 mg po (or equivalent dose of antihistamine).

Paracetamol 500-1000 mg po (or equivalent dose of antipyretic). |
| Grades 3 or 4
Grade 3:
Prolonged (i.e., not rapidly responsive to symptomatic medication and/or brief interruption of infusion); recurrence of symptoms following initial improvement; hospitalisation indicated for other clinical sequelae (e.g., renal impairment, pulmonary infiltrates)
Grade 4:
Life-threatening; pressor or ventilatory support indicated | Stop Infusion.
Additional appropriate medical therapy may include but is not limited to:
IV fluids
Antihistamines
NSAIDS
Paracetamol
Narcotics
Oxygen
Pressors
Corticosteroids
Epinephrine

Increase monitoring of vital signs as medically indicated until the patient is deemed medically stable in the opinion of the investigator.
Hospitalisation may be indicated.                                                                                                                                                                                                                                                                                                                                                                                          | No subsequent dosing                                                                                                                                                                                                                             |

| NCI CTCAE v5 Grade                                                                                                                              | Treatment                                                                               | Premedication at subsequent dosing |
|-------------------------------------------------------------------------------------------------------------------------------------------------|-----------------------------------------------------------------------------------------|------------------------------------|
|                                                                                                                                                 | Patient is permanently discontinued from further trial treatment administration. |                                    |
| Appropriate resuscitation equipment should be available in the room and a physician readily available during the period of drug administration. |                                                                                         |                                    |

